#### **2.7.4 Data and Specimen Storage and Transmission.**

The primary analysis for Nrf2 protein, mRNA, and antioxidant enzymes in cell pellets will be conducted in the laboratory of [name] at the Johns Hopkins University School of Public Health. Initial processing of the specimens will take place at each of the clinical sites. Cell pellets from bronchoalveolar lavage, endobronchial brushings, peripheral blood monocytes, and nasal epithelial cells will be frozen at -70C and shipped on dry ice in batches to the [name] laboratory for analysis. All of the laboratory methods have been well established in the [name] laboratory, and Nrf2 protein and message as well as antioxidant enzymes have been stable in frozen specimens.

The ancillary studies will be done with fresh alveolar macrophages and thus will be done on a subset of specimens. Measurement of bacterial phagocytosis and killing will be done at [name] laboratory at SUNY Buffalo and at [name] laboratory at Hopkins ( n = 120 samples (60 pairs)). Measurement of IL8 production by LPS stimulated macrophages and suppression by dexamethasone will be conducted on fresh specimens from Hopkins (n = 60 samples (30 pairs)).

Data, which includes identifiable personal health information (PHI), are collected at each of the clinical sites. PHI is stored at each of the clinical sites in accordance with HIPAA regulations and local university and hospital policies. This includes the storage of PHI in locked cabinets or rooms, limited access to secure data areas by certified participating study personnel, password protection for electronic medical records, and explanation of HIPAA regulations on the study consent form. Data such as lung function or laboratory tests that is collected as part of this study may be transmitted to the patients treating physicians with the consent of the participant. Participants are informed in the consent that PHI may also be disclosed for auditing purposes by the FDA or other regulatory bodies and is subject to subpoena.

PHI is not transmitted to the coordinating center or central laboratory in that all specimens and records are identified by an anonymous study ID, and other identifying information such as name or hospital ID number are not entered into the central study database. Source records that are transmitted to the coordinating center for data quality audits have identifying information redacted.

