## 2.2 Trial Schema

The trial will be a 3-arm parallel design randomized placebo-controlled trial in 90 COPD patients. After screening (V1), participants are scheduled for a baseline clinical evaluation (V2) and a bronchoscopy (V3) within a week. The clinical evaluation (V4) and bronchoscopy (V5) are repeated 4 weeks later. Although the effects of sulforaphane on nasal epithelium are known to occur within several days, the 4 week treatment period is long enough to permit the inflammatory response from the first procedure to subside and to provide an assessment of tolerability of the treatment.

[figure not shown]

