## 2.6 Study Data Collection schedule

The specific study procedures and approximate time commitment from the participant are shown below:

Participants will have 5 study visits over 4-8 weeks as follows:

Visit 1 (V1) (Day – 28 to -7) (2 hours) During this visit, the participant will provide informed consent, undergo eligibility screening questionnaire, lung function (spirometry before and after bronchodilators), Complete Blood Count, biochemistry panel including renal and liver function and electrolytes, TSH, urinalysis, and a pregnancy test for women of child-bearing potential.

Visit 2 (V2) (Day -14 to 0) (2-4 hours) During this visit, eligible participants will perform baseline spirometry, lung volumes, and diffusing capacity, and will complete general health questionnaires and respiratory specific questionnaires (ATS-DLD, SGRQ and MRC). A brief physical examination will be performed. Baseline biological specimens including blood for PBMCs will be performed.

Visit 3 (V3) (Day 0) (4 hours) The participant will have a baseline bronchoscopy for collection of bronchoalveolar lavage cells and nasal and bronchial epithelial brushings. Randomization eligibility will be established and the participant will be assigned to a masked treatment. After recovery from the bronchoscopy sedation, the participant will be given the assigned treatment which will consist of a coded container of capsules containing either placebo or one of the two doses of sulforaphane.

Phone Visit 1 (P1) (Day 1) (15-30 minutes) Patients are phoned the day following the bronchoscopy to determine whether they have had any adverse experiences, to re-instruct them in use of the medication, and to confirm future appointment dates and times.

Phone Visit 2 (P2) (Day 7-14) (15-30 minutes) Patients are contacted to determine their compliance with the medication and to report any adverse effects.

Visit 4 (V4) (Day 21 to 30) (2 – 4 hours) The participant will repeat the baseline spirometry, lung volumes and diffusion capacity, CBC, pregnancy test, urinalysis, TSH and biochemistry panel and have follow-up health status and adverse effect questionnaires and a brief physical examination. Follow-up collections of blood for biological measures are obtained.

Visit 5 (V5) (Day 22 to 31) (4 hours) Follow-up bronchoscopy for collection of bronchoalveolar lavage, nasal brushings, specimens and endobronchial brushings. Return of unused capsules for pill counts.

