## 4 Statistical Design and Sample size

### 4.1 Justification of Sample size

**Power Analysis:** For a one-way ANOVA, assuming 30 samples per each of 3 groups, and 80% power, the detectable effect size by Cohen's  $f$  statistic is 0.333, which corresponds to a medium effect size. The sample size is based on SD estimated from assays of human COPD lung tissues and nasal epithelial cells. The detectable fold-difference for primary and secondary analytes is listed in the table below. Estimates are also provided for a nominal type I error of 0.01 to account for multiple comparisons.

| Analyte      | Estimated SD
(Fold-change) | Effect Size (3 groups
of $n = 30$ , power =
0.80) |                 |
|--------------|-------------------------------|---------------------------------------------------------|-----------------|
|              |                               | alpha =
0.05                                         | alpha =
0.01 |
| Nrf2 protein | 0.198                         | 0.066                                                   | 0.080           |
| Nrf2 mRNA    | 1.007                         | 0.335                                                   | 0.406           |
| GTSM         | 0.397                         | 0.132                                                   | 0.160           |
| GSTP1        | 0.273                         | 0.091                                                   | 0.110           |
| HO-1         | 0.427                         | 0.142                                                   | 0.172           |
| NQO1         | 0.484                         | 0.161                                                   | 0.195           |

These effect sizes are highly plausible and have potential clinical importance insofar as they compare to changes of 1.25-4.00-fold in Nrf2 activity in control smokers vs. patients with COPD, and 2-3-fold changes in anti-oxidant enzymes induced by oral sulforaphane in control nasal epithelium. Tests for trend for these analytes vs. dose with 90 patients in 3 groups has 80% power with type I error of 0.05 to detect a correlation coefficient of 0.26 or greater.

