### 4.2 General Statistical Approach

**Primary analysis.** Baseline variables and outcome measures will be examined using descriptive and graphical displays such as boxplots and scatter plots. Appropriate transformations will be applied to data that is non-parametric. The primary analysis will be an unadjusted one-way ANOVA for fold-change in Nrf2 expression and phase II antioxidant levels with sulforaphane dose as the main effect. Post-hoc comparison between doses will use Tukey's test. Dose-response relationships will be tested with a test for trend (Pearson's  $r$ ). If significant imbalance occurs between groups, then general linear models will be constructed to adjust for baseline differences. The primary analysis will use the modified intention to treat paradigm.

**Secondary analyses.** Secondary outcome measures will be similarly analyzed, but p-values will be adjusted for multiple comparisons. Subgroups of interest (gender, smoking status, GOLD stage, adherent participants) will be examined by tests of treatment by subgroup interaction.

**Early stopping rules.** We are not proposing any interim efficacy analysis or early stopping rules.

Participants will continue to be enrolled in the trial regardless of whether they take the study medication, as our first analysis will be an intention to treat analysis. Secondary analyses will

include only adherent patients. Patients may be removed from the study if they sustain interim adverse events related to the study, if they are not healthy enough to undertake the study procedures (e.g. bronchoscopy).

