#### **4.4 Study Organization**

The study will be co-directed by Drs. [name] and [name] who will serve as the joint Principal Investigators. [name] will direct the clinical research aspects of the study and [name] will direct the laboratory-based aspects of the study. [name], with [name] will supervise the extraction, purification, analysis, and packaging of the sulforaphane. [name] will direct the data coordinating center and the acquisition and analysis of the data. Three clinical sites, each of which will be recruiting 30 patients, will be supervised at SUNY Buffalo by [name], at Temple by [name], and at Hopkins by [name]. The overall scientific direction of the study will be directed by the Scientific Steering Committee consisting of Drs. [name], [name], [name], [name], [name], and [name]. The two ancillary studies will be supervised by [name] (Sulforaphane Effect on Bacterial Phagocytosis) and [name] (Sulforaphane Effect on Steroid Sensitivity).

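### Bacterial clearance (H4) is assayed in two laboratories, but the stated model has no site or laboratory term, which can cost power (low severity; H4 is exploratory)

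*Protocol*

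**What the plan says.** Section 4.4 sets up the recruitment: "Three clinical sites, each of which will be recruiting 30 patients". Section 2.7.4 says the ancillary studies need fresh alveolar macrophages and so use a subset of specimens. Phagocytosis and killing (H4) are measured at a Buffalo laboratory and a Hopkins laboratory, on 120 samples or 60 pairs. For H5 the section reads "Measurement of IL8 production by LPS stimulated macrophages and suppression by dexamethasone will be conducted on fresh specimens from Hopkins", with 60 samples or 30 pairs. The Nrf2 and antioxidant assays behind the primary outcome use frozen pellets, processed first at the sites and then assayed in one central laboratory.

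On allocation, section 2.6 says only that at V3 "the participant will be assigned to a masked treatment". The text shown gives no ratio, block or stratum.

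On analysis, section 4.2 states: "The primary analysis will be an unadjusted one-way ANOVA for fold-change in Nrf2 expression", extended to the phase II antioxidants, with dose as the main effect. Secondary outcomes get the same treatment with p-values corrected for multiplicity. General linear models come in only if a significant imbalance is seen, to adjust for baseline differences. Site is named neither there nor among the subgroups. Section 2.5.2 lists the ancillary studies among the secondary outcomes and calls them exploratory.

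**The concern.** Fresh cells have to be assayed near where they are taken, and 60 pairs is exactly two sites of 30. So for H4, site and assay laboratory appear to be the same variable. Killing and phagocytosis assays run in two laboratories may differ in how large a response they register. If they do, a model with dose alone treats that difference as noise.

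What is at stake is power for H4. A secondary matter is H5. All of its patients come from one site, so its arm sizes depend on how assignment is balanced within that site, and the protocol does not say how this is done.

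**Working it through.** **The plan's own figure.** Section 4.1 works with "assuming 30 samples per each of 3 groups, and 80% power" and reports that Cohen's f "statistic is 0.333, which corresponds to a medium effect size". With noncentrality f² × N and a noncentral F on (2, 87) degrees of freedom, 80% power at alpha 0.05 needs f = 0.3329. The stated figure reproduces. It refers to all 90 patients; the protocol gives no power for the H4 or H5 subsets. By the same formula with perfectly equal arms:

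| Subset | n per arm | Detectable f (80% power) | Power at f = 0.333 |
|---|---|---|---|
| All patients | 30 | 0.333 | 0.80 |
| H4 | 20 | 0.41 | 0.61 |
| H5 | 10 | 0.60 | 0.32 |

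**H4 set-up.** Take two sites of 30, a change score with SD 1, and arm means of 0, 0.5 and 1 SD (high dose minus placebo = 1 SD).
- Variance of the arm means: (0.25 + 0 + 0.25)/3 = 0.167, so f = 0.41 and noncentrality = 60 × 0.167 = 10.
- With no laboratory difference, exact power for equal arms is 0.793 without a site term (2, 57 df) and 0.793 with one (2, 56 df). The term costs essentially nothing when it is not needed.

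**What a laboratory shift does.** Let the laboratories differ by D SD in the mean change score. Site then adds 60 × (D/2)² = 15D² to the residual sum of squares if it is left out. With arms balanced within site, the expected residual mean square becomes (57 + 15D²)/57. That is 72/57 = 1.26 at D = 1 and 117/57 = 2.05 at D = 2.

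**Simulated H4 power** (5,000 trials per case; a repeat with 12,000 trials agreed within about 0.01). The unbalanced columns use a 30/30/30 list over 90 patients without site strata.

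| D (assumed) | Unbalanced, no site term | Unbalanced, site term | Balanced by site, no site term | Balanced by site, site term |
|---|---|---|---|---|
| 0 | 0.80 | 0.79 | 0.79 | 0.79 |
| 0.5 | 0.77 | 0.78 | 0.77 | 0.79 |
| 1 | 0.69 | 0.78 | 0.70 | 0.80 |
| 2 | 0.47 | 0.78 | 0.38 | 0.78 |

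The mean estimate of the 1 SD effect stays at about 1.00 throughout. Type I error without balance stays near 0.05. With balance but no site term the test becomes conservative (0.02 at D = 1, 0.003 at D = 2). So the site term, not balance alone, recovers the power.

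**H5 arm sizes at one 30-patient site.** These apply only if assignment is not blocked within site. The first figure is for the 30/30/30 list without site strata, the second for simple randomisation.
- Exactly 10/10/10: 4% / 3%.
- Smallest arm 7 or fewer: 35% / 48%. Smallest arm 6 or fewer: 14% / 25%.
- Variance of a pairwise contrast relative to 10 versus 10: up 5% / 8% on average, and 29% / 42% at the 95th percentile. A 6 versus 14 split gives (1/6 + 1/14)/(2/10) = 1.19.
- For an effect with 80% power at 10/10/10 (f = 0.60, linear in dose), average power is about 79% / 78%.

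**Primary outcome.** If site explains a share r of the fold-change variance, including it raises the effective f to 0.333/√(1 − r). Power is 0.80 at r = 0, 0.81 at 2%, 0.82 at 5% and about 0.88 at 20%. The documents give no value for r.

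**The case against.** **Pairing.** The outcomes are changes within a patient. If both samples of a pair go to the same laboratory, a constant additive offset cancels in a difference and a constant multiplicative one cancels in a ratio. This stands. What remains is a laboratory difference in the size or spread of the change, and D above means only that.

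**Bias.** A reader might infer that unequal arms across laboratories would create a false treatment effect. Under randomisation such imbalance is chance. It adds variance and can distort one realised trial, but the simulation shows no systematic bias and no excess of type I error.

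**Allocation.** A reader might infer that assignment is not balanced within site. The protocol neither provides for stratification nor rules it out. Its 30 per group is a power assumption, and the list method may sit in a document not at hand. Only a request for confirmation is justified.

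**H5.** A reader might extend the laboratory argument to H5. With a single site, no between-site difference can enter its arm comparison. Its real limit is 30 patients, and balance changes little on average.

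**Primary outcome.** Those assays run in one central laboratory on a within-patient fold-change, so the site share may be close to zero.

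**Status and partial cover.** H4 and H5 are ancillary and exploratory, and applying the ANOVA to them rests on their listing under secondary outcomes. The conditional linear models in 4.2 could admit site, but they depend on observed imbalance and do not name it. All of this lowers the severity; none of it supplies the missing term for H4.

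**Conclusion.** The point holds for H4, at low severity. The stated analysis omits a factor that the design itself creates. For a 1 SD high-dose effect, H4 power drops from about 0.79 to about 0.68-0.69 at an assumed 1 SD laboratory shift in the change score and to 0.47 at 2 SD, against about 0.78-0.80 with the term. At a shift of zero nothing is lost either way.

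The result rests on three assumptions: the size of the shift, which the documents do not inform; both samples of a pair being assayed in the same laboratory; and H4 site and laboratory coinciding, which is inferred from the use of fresh cells and the 60 pairs.

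For H5 the exposure is unequal arm sizes only, at about 1 to 2 points of power on average if assignment is not blocked by site. For the primary outcome the gain from a site term is small, or nil if site explains little of the fold-change variance.

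**What to change.** - In 4.2, prespecify site as a factor in the H4 model and say that it also stands for assay laboratory. This costs one degree of freedom.
- In 4.2, include site as a factor in the primary model too. This costs two of 87 degrees of freedom, and the gain may be small.
- In 2.6 at V3, or by reference to the randomisation plan, confirm that masked assignment is blocked within clinical site, so that the Hopkins patients who carry H5 split about 10/10/10. If the list is already built that way, one sentence is enough; if not, the coordinating centre's list changes.

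No extra patients, samples or procedures are needed.

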### **3. Study Treatments**

#### **3.1 Assigned treatments**

1. 25 micromoles (4.4 mg) sulforaphane once daily by mouth
2. 150 micromoles (26.6 mg) sulforaphane once daily by mouth
3. Placebo (microcellulose) once daily by mouth

### **3.2 Drug Production and packaging / FDA Approval**

Sulforaphane will be prepared under the direction of Drs. [name] and [name] in accordance with GMP using procedures that have been well described. Briefly, the procedure, performed in an FDA-certified facility, uses a hot-water pulverization and extraction of glucosinolates from standardized patented broccoli sprouts. (Broccosprouts®, Tracy, CA) The extract is treated with myrosinase from daikon sprouts to form the isothiocyanate. The homogenate is lyophilized and pulverized, and stored as a frozen powder. After analysis of sulforaphane concentration by cyclocondensation, the material is encapsulated at the two dose levels at a GMP manufacturing pharmacy and backfilled with methylcellulose. Similar capsules are filled with methylcellulose alone to serve as placebos. Study drug is stored at -20 C under which conditions the drug is known to be stable for at least one year until it is dispensed and thereafter is maintained in a refrigerator for the 4 week duration of the study. Because the material is hygroscopic, we are recommending that it be stored in a refrigerator during the 4 weeks of the trial, although we are not certain that this is an absolute requirement. The trial will be conducted under an IND (#109233) held by [name]

Participants will be provided with a one month supply of treatment at randomization. Distribution, auditing and maintenance of treatment inventories at the clinical centers including monitoring of expiration dates will be managed as a feature of the data system.

### **3.3 Side effects of study treatments**

Ingestion of Broccoli Sprout Extract (BSE) containing sulforaphane is thought to be of minimal risk to individuals given the fact that broccoli and broccoli sprouts are widely consumed throughout the world and are without known adverse effects. Sulforaphane in the precursor glucosinolate form is widely available as a nutritional supplement in health food stores. However, the intestinal conversion to sulforaphane in the isothiocyanate form may be variable, depending on the intestinal flora, so we have elected to use the highly purified and quantified form for this trial. To date, there are no known significant adverse effects related to ingestion of the substance.

### **3.4 Unmasking**

Drug and placebo will be supplied in similar appearing capsules, back-filled with methylcellulose to approximate similar appearance and weight. Neither the participant nor the site investigators or the laboratory personnel will know the identity of the drug assignment. Emergency unmasking can take place by opening a sealed envelope that is distributed with the drugs. All unmasking events are reported to the DCC. The sealed envelopes are returned to the DCC at the end of the trial. Also, the investigators doing the bioassays will do them masked to treatment assignment. It is our general position that unmasking of treatment assignment is rarely necessary. If adverse events occur that may be related to the study treatment, then the study treatment is stopped and the patient is followed on an intention to treat basis. Envelopes with treatment assignment are provided to the clinic in the case a treating physician feels it is important to know the treatment assignment.

### **3.5 Routine COPD Treatment**

All participants will be able to continue with their routine COPD care which largely consists of long-acting bronchodilators and inhaled corticosteroids. The only change that we are asking our participants is to limit their intake of cruciferous vegetables to no more than one serving per week. Based on food-frequency information in COPD patients, this should not represent an

undue burden and will be easy for most to adhere to. Participants will be given a flashcard listing cruciferous vegetables.

## 4 Statistical Design and Sample size

### 4.1 Justification of Sample size

**Power Analysis:** For a one-way ANOVA, assuming 30 samples per each of 3 groups, and 80% power, the detectable effect size by Cohen's  $f$  statistic is 0.333, which corresponds to a medium effect size. The sample size is based on SD estimated from assays of human COPD lung tissues and nasal epithelial cells. The detectable fold-difference for primary and secondary analytes is listed in the table below. Estimates are also provided for a nominal type I error of 0.01 to account for multiple comparisons.

| Analyte      | Estimated SD
(Fold-change) | Effect Size (3 groups
of $n = 30$ , power =
0.80) |                 |
|--------------|-------------------------------|---------------------------------------------------------|-----------------|
|              |                               | alpha =
0.05                                         | alpha =
0.01 |
| Nrf2 protein | 0.198                         | 0.066                                                   | 0.080           |
| Nrf2 mRNA    | 1.007                         | 0.335                                                   | 0.406           |
| GTSM         | 0.397                         | 0.132                                                   | 0.160           |
| GSTP1        | 0.273                         | 0.091                                                   | 0.110           |
| HO-1         | 0.427                         | 0.142                                                   | 0.172           |
| NQO1         | 0.484                         | 0.161                                                   | 0.195           |

These effect sizes are highly plausible and have potential clinical importance insofar as they compare to changes of 1.25-4.00-fold in Nrf2 activity in control smokers vs. patients with COPD, and 2-3-fold changes in anti-oxidant enzymes induced by oral sulforaphane in control nasal epithelium. Tests for trend for these analytes vs. dose with 90 patients in 3 groups has 80% power with type I error of 0.05 to detect a correlation coefficient of 0.26 or greater.

